#### Randomization

On the day of the randomization visit, patients were confirmed to meet eligibility criteria, enrolled into the trial, and randomly allocated to either receive high volume online HDF or continue high-flux HD for 6 months and be observed for the next 12 months. Sequence generation for the randomized allocation was performed in a centralized manner by the EPICENTER ACRO using Microsoft Excel; the randomization allocation was uploaded into REDCap for assignment. The investigators’ staff performed the randomization via the REDCap™ (https://www.project-redcap.org) electronic case report form (eCRF) and assigned patients to either arm. Because of the nature of the intervention, the investigators and local clinical staff could not be blinded to treatment assignment.

Before initiation of the interventional treatments (high volume online HDF or high-flux HD), baseline values for clinical, laboratory, and quality of life parameters were collected at the randomization visit. These included capturing clinical parameters (weight, systolic and diastolic blood pressures (SBP/DBP), and pulse), performance of a bioelectrical impedance body composition assessment using the Body Composition Monitor (BCM; Fresenius Medical Care, Bad Homburg, Germany) [30, 31] before dialysis, collection of blood samples, administration of the HRQOL questionnaires (KDQOL, self-reported dialysis recovery time, thirst questionnaire), recording the participants medical history (including presence of comorbidities and etiology of kidney disease), concomitant medications, and dialysis treatment characteristics (treatment time, ultrafiltration volume (UFV), substitution volume for HDF, urea distribution volume, estimated adequacy (single pool Kt/V), blood flow rate (Qb)). After initiation of the interventional treatments, adverse events were actively assessed by the investigators, and safety data was collected as applicable.

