Investigators and clinical professionals at each participating center were trained by the study team in a standardized fashion to ensure there was homogeneity in dialysis treatment and study procedure. Routine study meetings are being performed for continuing training. This protocol recommends a standardized dialysis protocol following the current guidelines both for high flux HD or high volume online HDF. Postdilution high volume online HDF is being performed using the Fresenius 5008 CorDiax HDF machine with the AutoSub plus function and high-flux HD is being performed using the Fresenius 4008S machine. The recommended composition of the substitution fluids and dialysate was: sodium 138 mEq/L, potassium 2 mEq/L, calcium 1.5 mmol/L, dry bicarbonate 32 mEq/L and glucose 5.5 mmol/L. Dialysis needle size was standardized for high volume online HDF. For high volume online HDF, sterile and nonpyrogenic substitution fluids were produced by ultrafiltration of the ultrapure dialysate. The HD group also used ultrapure dialysate. Ultrapure quality was defined as bacterial counts < 0.1 CFU/mL and endotoxin levels < 0.025 EU/mL. Fresenius Polysulfone HDF 100 dialyzers are being used for high volume online HDF treatments and Fresenius FX Classix 100 dialyzers are being used for HD treatments. The intended dialysis treatment duration for both modality arms of the trial was 240 min. For the high volume online HDF arm, dialysis is being performed in the post-dilution mode with a target convection volume of 22 L/treatment.

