### Power analysis

Data will be analyzed according to an intention-to-treat principle (i.e. according to assigned instead of received treatment). The primary endpoint is steps per 24 h beginning at the start of each dialysis treatment on dialysis days and concurrent times on non-dialysis days in patients treated with high volume online HDF versus high-flux HD. With an enrollment target of 110 participants in each arm (considering a drop out of 20%) we estimated the 86 patients will complete the follow up in each arm, which will provide the trial a 90% power to detect a 20% effect with respect to the primary outcome (predefined as a 20% increase in average total steps at the dialysis day in the high volume online HDF group compared to the high flux HD group).

In addition, near the end of the baseline period we confirmed the power calculation using interim baseline data (*n* = 142); this computation suggested that enrollment of 120 subjects would be anticipated to detect a 10% effect with respect to the primary outcome with 90% statistical power, and with 90 subjects it would be anticipated to detect an effect with respect to the primary outcome with 80% statistical power.

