The hypothesis driven outcomes of this study include the:Primary outcome: the difference in the change in steps per 24 h on dialysis days (captured by a triaxial accelerometer and in reference to the start time of the dialysis) from baseline to the 6-month follow up in patients treated with high volume online HDF versus high-flux HD.Secondary outcome: the difference in the change in KDQOL scores (total, PCS and MCS) and self-reported dialysis recovery time from baseline to the 6-month follow up in patients treated with high volume online HDF versus high-flux HD.Various exploratory and subgroup outcomes will also be assessed to investigate hypotheses.

For the primary outcome of step counts per 24 h, we plan to use an intention-to-treat design to determine the effect of the intervention using linear mixed effects model comparing mean changes from baseline between treatment groups at months 3 and 6 with data presented in box-plots and histograms for the baseline, 3- and 6-month study periods. Similar methods will be used to assess exploratory HRQOL and other outcomes. Further evaluation of statistical interaction between the treatment effect on primary outcome may be performed for age, sex, body composition and other parameters.

An exploratory as-treated analysis may also be performed on the primary outcome, which will be restricted to those that achieved the target convection volume of 22 L per treatment at most dialysis sessions and did not miss a remarkable proportion of their dialysis treatments. This analysis will be performed using the same methods as the intention-to-treat analysis. Adjustments may be performed to the analysis via inverse probability weighting and g-estimation methods.

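### The optional as-treated analysis filters on a 22 L convection volume that only the HDF arm can reach, and adjustment for that one-sided selection is left optional

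*Protocol article*

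**What the plan says.** The main analysis is not in doubt: "Data will be analyzed according to an intention-to-treat principle" (Power analysis), and Statistical design repeats this for the primary outcome, the change in steps per 24 h on dialysis days.

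Statistical design then adds a further, optional analysis: "An exploratory as-treated analysis may also be performed on the primary outcome". Two conditions define who enters it:

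- volume: "restricted to those that achieved the target convection volume of 22 L per treatment at most dialysis sessions";
- attendance: "and did not miss a remarkable proportion of their dialysis treatments".

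On method it says: "This analysis will be performed using the same methods as the intention-to-treat analysis". On correction for selection it says: "Adjustments may be performed to the analysis via inverse probability weighting and g-estimation methods".

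The volume target is defined under Dialysis, machines, and equipment: "For the high volume online HDF arm, dialysis is being performed in the post-dilution mode with a target convection volume of 22 L/treatment". Among the treatment characteristics listed under Randomization, the matching item is "substitution volume for HDF". No delivered-dose criterion for the HD arm is given in the as-treated definition.

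**The concern.** A volume criterion that exists in one arm cannot define a two-arm analysis set. Either the comparator disappears, or one arm is screened on something that happened after randomisation while the other is not. In the second case the patients compared are no longer those whom randomisation made comparable. Whatever determines who reaches the volume, such as access, blood flow or session length, may also relate to how a patient's activity changes over six months.

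Fitting the intention-to-treat mixed model to the filtered set does not restore comparability. The methods that could do so, weighting and g-estimation, are named but not required, so the plan permits the unadjusted contrast to stand alone. At stake is the interpretation of the only on-treatment estimate of the primary outcome that the article describes, in a trial whose Discussion already recognises possible bias from the lack of blinding.

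**Working it through.** **1. Reading the rule against the arms.** The article states no figure for this analysis, so there is none to reproduce. The check is which patients can satisfy each condition.

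| Condition | HDF arm | HD arm |
|---|---|---|
| 22 L at most sessions | can be met or missed | no target set; cannot be met |
| Attendance | applies | not limited to one arm, so may apply |

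- Literal reading (both conditions for everyone): the HD arm is empty and there is no contrast.
- Practical reading (volume for HDF, attendance for both): HDF patients are selected on volume and attendance, HD patients on attendance alone.

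On either reading the volume condition is one-sided.

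**2. How large the resulting bias could be (illustration).** Suppose HDF has no effect, no adjustment is made, and attained volume and change in steps are jointly normal in the HDF arm.

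Inputs:
- *p*, share of HDF patients retained: not in the documents; assumed 0.7.
- *r*, correlation of attained volume with change in steps: not in the documents; assumed 0.1 to 0.4.
- Patients per arm: 195 enrolled (Study status and timeline) less the planned 20% drop-out (Power analysis), split equally: 195 × 0.8 / 2 = 78.

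Formulas, with φ and Φ the standard normal density and distribution function:
- bias in SD units = r × φ(z) / p, where z is the (1 − p) quantile;
- SE in SD units = √(1/(78p) + 1/78), ignoring the slight loss of variance from truncation;
- rejection rate of a two-sided 5% test = Φ(bias/SE − 1.96) + Φ(−bias/SE − 1.96).

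For p = 0.7: z = −0.524, φ(z) = 0.348, φ(z)/p = 0.497. Retained HDF patients = 54.6, so SE = √(1/54.6 + 1/78) = 0.176.

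| r | Bias (SD) | Bias/SE | Rejection rate with no effect |
|---|---|---|---|
| 0.1 | 0.050 | 0.28 | 5.9% |
| 0.2 | 0.099 | 0.56 | 8.7% |
| 0.3 | 0.149 | 0.84 | 13.5% |
| 0.4 | 0.199 | 1.13 | 20.3% |

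A negative *r* of the same size gives the mirror image: a spurious disadvantage for HDF with the same rejection rate.

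**3. Sensitivity to the assumed inputs.** Using the planned 86 completers per arm instead of 78, and r from 0.1 to 0.3:

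- p = 0.9: bias 0.02 to 0.06 SD, rejection rate 5.2% to 6.6%.
- p = 0.5: bias 0.08 to 0.24 SD, rejection rate 7.1% to 24.9%.

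The bias is negligible if nearly everyone reaches the target and material if half do.

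**The case against.** **The analysis is already exploratory and optional.** This is true, and it limits the weight of the point. The primary result and its error rate are untouched.

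**The right methods are already named.** Inverse probability weighting and g-estimation address this kind of selection. That softens the problem. It does not remove it, because the default is the same model as intention-to-treat and the correction is discretionary.

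**Details belong in the analysis plan.** A numeric attendance cut-off and the full list of weighting covariates are commonly left there, so their absence from an article is no fault. The one-arm volume rule is different: it is stated, and as stated it does not define a usable comparison.

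**HD patients are selected too.** A reader might infer that filtered HDF patients are set against wholly unselected HD patients. The text does not support that. The attendance condition is written without an arm restriction, so HD patients are unselected only on delivered dose.

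**The direction of bias is not shown.** It is tempting to say that the comparison favours HDF because patients who reach the volume are fitter. The outcome is change from baseline, which largely removes a stable difference in fitness; bias requires that reaching the volume predicts *change* in steps. Eligibility (adequate access flow, Kt/V of at least 1.2, no non-adherence or severe mobility limitation), a common intended session length of 240 min and standardised HDF needle size also narrow the likely drivers. This stands: the contrast is open to bias, but the documents do not establish its sign or size.

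**Conclusion.** The point holds in a limited form. The as-treated rule rests on a criterion that only one arm can meet. Taken literally it leaves no comparator; taken as intended it yields a contrast that randomisation no longer protects, with correction left to discretion.

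The figures of about 0.05 to 0.20 SD, and an error of about 6% to 20% in place of 5%, are illustrations. They rest on an assumed 70% retained, an assumed correlation of 0.1 to 0.4 with change in steps, 78 patients per arm, no true effect and no adjustment. They are not estimates for this trial.

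Two stronger conclusions should not be drawn. Nothing here weakens the intention-to-treat primary analysis. Nor do the documents suggest that the as-treated result would be put forward in place of a null primary result. The correction is modest, but worth making because it is cheap.

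**What to change.** In Statistical design:

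1. State that the volume criterion applies to HDF patients only, and that HD patients are retained subject to the same attendance rule as HDF patients.
2. If the analysis is run, require one of the following:
   - inverse probability weighting of the retained patients on baseline predictors of reaching the target, for example access type, blood flow rate, treatment time and baseline steps, all taken before allocated treatment starts; or
   - g-estimation on delivered convection volume with both arms kept whole, stating the value assigned to HD patients and the assumed relation of effect to volume.
3. Do not report the unadjusted restricted contrast as a treatment effect.

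An instrumental-variable estimate with a yes/no exposure of HDF at target should not be substituted. It assumes that HDF delivered below 22 L has no effect; if it does have one, the estimate is distorted.

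The cost is wider intervals and some extra analysis work. No new data are needed: access type and baseline activity are recorded in the run-in, blood flow and treatment time at randomisation, and treatment characteristics from each session during follow-up.

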#### Key roles

The role of the study investigators was to assist with the design of the protocol and is to perform the medical oversight of the conduct of the study. Site investigators are directly performing and orchestrating the collection of study data at their sites during the trial. The principal investigator of the trial is providing medical oversight of the study conduct at all sites under the guidance of the steering committee and orchestrating the management of the study.

The role of the proponent institution Pontifícia Universidade Católica do Paraná is supporting the study with the infrastructure for the study management through use of the university’s academic clinical research organization, hosting of the REDCap eCRF on the university’s server, and use of the university’s central ERB and Research Council.

The role of the outpatient dialysis centers is permitting clinical research at the clinics and providing support of their clinical staff for the data collection and conduct of study procedures under the oversight of the site investigators and local trial leadership.

The role of the company Fresenius Medical Care is providing the sites with the infrastructure of HDF machines, providing the dialysis supplies during the study, as well as providing BCM machines as needed for the conduct of the study. Also, they are supporting the trial by providing some staff for monitoring of study sites. Furthermore, Fresenius Medical Care is providing a monetary award to PUCPR’s academic clinical research organization (EPICENTER) performing the central management, data acquisition, monitoring of the trial. Fresenius Medical Care and the subsidiary company Renal Research Institute are also providing support from statistical experts to assist in the analysis of trial data under the oversight of the steering committee. Moreover, Fresenius Medical Care has supported three investigator meetings, as well as three steering committee meetings. The leadership of Fresenius Medical Care reviewed and approved the protocol prior to commencement.

The role of the steering committee members that represent all supporting institutions is to review and approve the research design, protocol, addendums and changes to the protocol, analyses, and publications of study data, as well as provide oversight of the conduct and safety of the study.

## Discussion

We initiated a multi-center RCT that will characterize for the first time objectively measured physical activity levels in ESRD patients treated by high volume online HDF versus high-flux HD. One of the novel attributes of this study is that it will capture granular physical activity data in reference to the time of dialysis treatments. This approach will allow for the assessment of peridialytic differences during recovery from a chronic dialysis treatment. Furthermore, this study will define profiles of HRQOL in ESRD patients treated by the modalities of high volume online HDF versus high-flux HD and allow for the exploratory investigation of whether self-reported HRQOL is associated with physical activity levels. Other exploratory investigations will investigate the impact of modality and role of physical activity levels on various outcomes related to medication use, clinical characteristics, intradialytic events, hospitalizations, and deaths. Ultimately, this investigation will elucidate whether treatment of ESRD patients with high volume online HDF is associated with patients having higher vitality, a better quality of life, and less negative outcomes as compared to those treated with high-flux HD.

The design of this study has many strengths that include being a multicenter RCT with enrollment targets able to achieve the power needed to make sound comparisons for outcomes in a patient sample representative of the dialysis population in the south and southeastern regions of Brazil with a dialysis vintage less than two years. Of note, about 50% of the dialysis population in Brazil resides in the southern part of the country [47]. Furthermore, this is the first study to the knowledge of the authors to investigate granular physical activity levels based on the time of intensive treatments in a chronically diseased population. Moreover, the array of self-reported, clinical and laboratory outcomes makes this study unique in the ability to investigate various outcomes in patients treated with high volume online HDF or high-flux HD.

Although our study design has many strengths, there are some possible limitations that include a potential for variations with self-reported outcomes and a possibility of undercounting of physical activity levels due to the ActiLife software default algorithm that was validated in younger patients performing exercise [45, 46]. Our examination of the low-frequency-extension filter algorithm available with the ActiLife software identified evident overcounting, which is consistent with previous reports in elderly populations [48]. Nonetheless, physical activity will have internal consistency in this well controlled study. Another potential limitation of the trial is related to the unblinded study design, which could have potentially introduced bias depending on provider perceptions of HDF and the quality of the provider-patient relationship.

## Conclusions

We have thoroughly detailed the description of the HDFIT study design, methods and protocol. Ultimately, this RCT will characterize granular physical activity levels based on the timing of chronic dialysis treatments and various self-reported, clinical and laboratory outcomes in ESRD patients treated by high volume online HDF versus high-flux HD. The results of this study will provide novel insights into the impacts of routine dialysis therapies and modalities and characterize ESRD patient profiles during the recovery period after dialysis.

## Abbreviations

ACRO: Academic clinical research organization
ADL: Activities of daily living
ALT: Alanine aminotransferase
Anti-HBs: Hepatitis B surface antibody
Anti-HCV: Hepatitis C antibody
BCM: Body composition monitor
BUN: Blood urea nitrogen
CKD: Chronic kidney disease
CPM: Counts per minute
CVD: Cardiovascular disease
DBP: Diastolic blood pressure
eCRF: Electronic case report form
ERB: Ethics review board
ESRD: End stage renal disease
HBsAg: Hepatitis B surface antigen
HD: Hemodialysis
HDF: Hemodiafiltration
HRQOL: Health related quality of life
ICF: Informed consent form
ICH: International Conference on Harmonisation
iPTH: intact parathyroid hormone
KDQOL: Kidney Disease Quality of Life
Kt/V: Dialysis adequacy
MAR: Missing at random
MCAR: Missing completely at random
MCS: Mental composite score
MET: Metabolic rates
MMW: Middle-molecular weight
MNAR: Missing not at random
MVPA: Moderate to vigorous physical activity
PCS: Physical composite score
Qb: Blood flow rate
RCT: Randomized control trial
RRT: Renal replacement therapy
SBP: Systolic blood pressure
TSAT: Transferrin saturation
UFV: Ultrafiltration volume
URR: Urea reduction ratio
